##### Spatiotemporal Parameters of Gait

Spatiotemporal parameters of gait will be evaluated to explore whether the addition of the “Brain-IT” training to usual care effectively improves gait. The gait of individuals with mNCD differs from that of healthy controls in terms of (among others; 1) slower single-task gait speed at the preferred walking speed (m/s) [18,168], (2) longer stride duration (ms) [18,168], (3) shorter stride length (cm) [18,168], (4) longer stance time (ms) [168], (5) longer swing time (ms) [168], (6) longer single support time (ms) [168], and (7) longer double support time (ms) [168]. Furthermore, individuals with mNCD typically show greater variability and coefficient of variation of gait parameters compared with cognitively healthy individuals [168].

According to the literature summarized above, we assume that an effective intervention leads to an (1) increase in single-task gait speed at the preferred walking speed, (2) decrease in stride duration, (3) increase in stride length, (4) decrease in stance time, (5) decrease in swing time, (6) decrease in single support time, and (7) decrease in double support time.

On the basis of this, we have elaborated our alternative hypotheses in more detail. It is hypothesized that in older adults with mNCD, the addition of the “Brain-IT” training to usual care results in differing effects on (c_1_) single-task gait speed at the preferred walking speed, (c_2_) stride duration, (c_3_) stride length, (c_4_) stance time, (c_5_) swing time, (c_6_) single support time, and (c_7_) double support time compared with usual care.

Spatiotemporal gait parameters will be assessed using a BTS G-WALK (BTS Bioengineering SpA, Garbagnate Milanese, Italy) inertial sensor attached with semielastic belt to participants’ lower back. The BTS G-WALK sensor delivers valid [169-171] and reliable [169,172] spatiotemporal gait parameters. All the acceleration data will be sampled at a frequency of 100 Hz. Data will be transmitted for analysis through Bluetooth 3.0, connection to the software program BTS G-Studio (BTS Bioengineering SpA, Italy). A gait-analysis protocol consisting of a figure of 8 walking path (ie, distance between cones of approximately 8 m) will be applied [108]. At least 50 consecutive gait cycles are required to ensure the reliability of the spatial and temporal parameters of gait variability [173]. Therefore, participants will perform 5 to 10 repetitions of the figure of 8 walking path at the preferred walking speed, depending on their walking speed and stride length. Comparative quantitative reference values for healthy older adults are available [174].

##### IADL Functioning

IADL functioning will be assessed using the Amsterdam IADL questionnaire short version, German for Switzerland, which has demonstrated good psychometric properties [109]. In addition, the original version of the Amsterdam IADL questionnaire was sensitive to longitudinal changes [175] and has been recommended for use in research settings [176]. The closest informant (eg, spouse, child, or friend) will fill out the questionnaire twice (within 2 weeks before the study participant starts or completes the intervention). Each item is scored on a 5-point Likert scale (“no difficulty” to “unable to perform”). Scoring is based on the item response theory. Item response theory latent trait levels are transformed to a T-score, with a range from 20 to 80, a mean of 50, and an SD of 10. A higher *t* score indicates better functioning [109].

##### Psychosocial Factors

QoL will be evaluated in interview format using the Quality of Life-Alzheimer Disease (QOL-AD) scale [110]. The QOL-AD is a valid and reliable self-report 13-item scale assessing various domains of QOL in cognitively impaired patients [110,177]. The German version of the QOL-AD scale, which has high test-retest reliability and good construct validity [111,112] will be used. Administration and evaluation will follow standardized instructions [112,178]. Comparable values are available for individuals with mNCD [179].

Levels of depression, anxiety and stress will be assessed using the short version of the Depression, Anxiety and Stress scale-21 (DASS-21) [113-115]. The DASS-21 has high reliability and good convergent and discriminant validity [113,180]. The validated German version of the DASS-21 will be administered and scored according to guidelines and scoring template [116,117]. Normative data of the 3 subscales are available and suggest cut-off scores of 10, 8, and 15, indicating significant depression, anxiety, or stress, respectively [116]. Comparative values for individuals with mNCD are available [181].

##### Cardiac Vagal Modulation (Resting Vagally-Mediated Heart Rate Variability)

To determine resting vm-HRV, all participants will be instructed to sit in a comfortable position on a chair without speaking, both feet flat on the floor with knees at a 90º angle, hands on the thighs (ie, palms facing upward), and eyes closed [95]. Measurements will be performed in a quiet room with dimmed light at room temperature. Data will be collected using a heart rate monitor (Polar M430) and sensor (Polar H10). The initial acclimatization phase will last for 5 minutes followed by a 5-minute resting measurement, the recommended standard duration for short-term recordings [95,182]. The start of the resting measurement will not be announced to the participants [95].

For resting HRV measurements, a sampling rate of 1000 Hz will be used to provide a temporal resolution of 1 milliseconds for each RR interval [183]. R-R data recordings will directly be transmitted to the Kubios HRV Premium (Kubios Oy, Kuopio, Finland, version 3.4) for analysis. Kubios HRV is a scientifically validated software for HRV analysis and has achieved the gold standard status in research [118,184-186]. The automatic beat correction algorithm and noise handling provided by the software will be used to correct for artifacts or ectopic beats. This algorithm has been validated for measurements at rest [184]. After removing interbeat-interval time series nonstationarities by detrending analysis using the smoothness priors method approach (settings: detrending method=smoothing priors, Lambda=500, f_c_=0.035 Hz), the mean values of mainly vagal-mediated HRV indices will be calculated for each segment. For this purpose, the mean R-R time intervals (mRR; ms), root mean square of successive RR interval differences (ms), percentage of successive RR intervals that differ by more than 50 milliseconds (%), absolute power of the high-frequency (0.15-0.4 Hz; high frequency [HF]) band (ms^2^), relative power of HF (in normal units; HF [n.u.] = HF [ms^2^] / (total power [ms^2^]—very low frequency; 0.00-0.04 Hz [ms^2^]), and Poincaré plot SD perpendicular to the line of identity (SD1; ms) will be considered [95,182,187-189]. In addition, the parasympathetic nervous system tone index (parasympathetic nervous system index) will be calculated to compare parasympathetic nervous system activity with normal resting values [189].

#### Other Endpoints

##### Safety Endpoint Variables

A protocol will be kept of all (serious) adverse events.

##### Baseline Factors

Baseline factors are collected through demographic data, including age, sex, height, weight, BMI, years of education, physical activity behavior (ie, measured with the German version of the International Physical Activity Questionnaire Short Form—short form [190,191] and analyzed according to published guidelines for data processing and analysis of International Physical Activity Questionnaire Short Form—short form [192]), clinical subtype (ie, mNCD due to AD, mild Frontotemporal NCD, mNCD with Lewy Bodies, or mild vascular NCD), medication intake, and changes in medication intake between pre- and postintervention measurements.

##### Adherence and Compliance Protocol

For the intervention group (ie, exergame training):

Adherence Protocol (number of sessions completed per week per participant; automatically assessed in the Exergame Training Software) to calculate the mean adherence rate (%) = number of training sessions attended / total number of training sessions offered; calculated as the average of each participant’s weekly adherence with a maximum of 100%.Compliance Protocol (training time completed per week per participant; automatically assessed in the Exergame Training Software) to calculate the mean compliance rate (%) = training duration attended (min) / total training duration offered (min), calculated as the average of each participant’s weekly compliance, with a maximum of 100%.

### Participant Timeline

Table 3 provides an overview of the participant timeline.

**Table 3 table3:** Participant timeline.

Time	≥2 days before premeasurements	≥1 day before premeasurements	Week−1 to 0	Week 1-12	Week 13-14	Week 15
Visit	Information	Consent and screening	Premeasurements	Intervention period	Postintervention measurements	Postintervention information
Location	At the interested persons’ home or at one of the study centers, depending on their preferences	At the interested persons’ home or at one of the study centers, depending on their preferences	At one of the study centers	At the participants’ homes	At one of the study centers	At the participants’ homes or at one of the study centers, depending on their preferences
Oral and written information	✓					
Written informed consent		✓				
Inclusion and exclusion criteria		✓				
Primary outcome:Qmci^a^ (~5 min)			✓		✓	
Secondary outcomes: WMS-IV-LM^b^ (~15 min) PEBL^c^-DSF^d^ and DSB^e^ (~5 min) PEBL-TMT-A and B^f^ (~5 min) TAP Go-NoGo^g^ (~5 min) HOTAP-A^h^ (~5 min) PEBL-MRT^i^ (~5 min) MRI^j^-Scan (~60 min) gait Analysis (~5 min) IADL^k^ (~15 min) QOL-AD^l^ (~5 min) DASS-21^m^ (~5 min) resting vm-HRV^n^ (~12 min)			✓		✓	
Baseline Factors (~5 min)			✓			
Safety endpoints			✓	✓	✓	
Adherence and Compliance to the Training Protocol				✓		
Study intervention				✓ (Study visits only applicable for exergame-group)		
Discuss individual results						✓

^a^Qmci: quick mild cognitive impairment screen.

^b^WMS-IV-LM: subtest “logical memory” of the Wechsler Memory Scale–fourth edition.

^c^PEBL: psychology experiment building language.

^d^DSF: digit span forward.

^e^DSB: digit span backward.

^f^TMT-A and B: Trail Making Test Part A and B.

^g^TAP Go-NoGo: subtest “Go-NoGo” of the test of attentional performance.

^h^HOTAP-A: HOTAP picture-sorting test part A.

^i^MRT: mental rotation task.

^j^MRI: magnetic resonance imaging

^k^IADL: instrumental activities of daily living.

^l^QOL-AD: Quality of Life-Alzheimer Disease.

^m^DASS-21: Depression, Anxiety and Stress scale-21.

^n^vm-HRV: vagally-mediated heart rate variability.

### Sample Size

The optimal sample size was justified based on Whitehead et al [193], and the following assumptions: the future main (full-scale) RCT will be planned with identical design and primary outcome as this study, with a two-sided type 1 error rate of 5% and a statistical power of 80%.

Our pilot feasibility RCT revealed a medium effect size (η^2^_p_=0.080; under peer review; registered at ClinicalTrials.gov NCT04996654). The observed medium effect size is slightly higher than the pooled evidence of exergame-based or combined motor-cognitive training interventions in older adults with NCD on global cognitive functioning. For exergame-based interventions in individuals with mNCD, Wang et al [194] reported a medium SMD of 0.57 (*P*=.21, 95% CI −0.32 to 1.47; *k*=1; n=20, compared with cognitively active control), while Gavelin et al (2021) reported an SMD of 0.13 (*P*>.05, 95% CI −0.22 to 0.48; *k*=2; n=109, compared with passive control) [63]. Stanmore et al [195] reported a small pooled effect of Hedges *g*=0.340 (*P*=.02, 95% CI 0.06-0.62; *k*=6; n=193) for patients with cognitive impairment. Further meta-analytic results for individuals with mNCD are limited to simultaneous motor-cognitive training with reported small-to-medium effect sizes, including SMDs of 0.45 [61], 0.48 [196], 0.531 [61], and 0.69 [197]. On the basis of this, a medium effect size of a SMD of 0.5 seems reasonable and is anticipated. This leads to a justified optimal sample size of n=14 per arm.

In our pilot feasibility RCT, we observed an attrition rate of 20% (under peer review, registered at ClinicalTrials.gov NCT04996654). This is consistent with recent systematic reviews synthesizing mean attrition rates of 17% (range, 0 to 59%) [198] in physical training interventions, 10% for combined motor-cognitive training interventions [199], and 15% (range 0%-31%) [200] for exergame-based interventions for patients with m-MNCD. Therefore, an attrition rate of 20% is anticipated. To ensure an adequate number of participants, a wide upper safety margin for an attrition rate of up to 40% is selected.

On the basis of these considerations, we will aim to recruit 17 to 20 older adults with mNCD per group, leading to a total sample size of 34 to 40. This will provide a sufficiently precise estimate of the treatment effect to minimize the sample size needed for a future full-scale RCT [193].

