### Randomization

#### Sequence Generation

Participants will be randomly allocated to the intervention or control group. Variable block randomization (ie, block sizes=4, 6, and 8) with a 1:1 allocation ratio stratified by sex and institute (study center) will be used.

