### Statistical Methods

Statistical analysis will be executed using R (The R Foundation), in line with RStudio (RStudio Inc). For demographics as well as training adherence and compliance, all collected data will be included (ie, including data of dropouts up to the time point of their withdrawal). For primary and all secondary outcomes, the data of all participants who completed pre- and postintervention measurements, regardless of protocol adherence, will be included in the statistical analyses. Questionnaire scores will be regarded as ordinal data. Data will be reported as mean (SD) values for continuous parametric data and median (IQR) values for continuous nonparametric data.

For all outcomes, descriptive statistics will be computed first. Normality distribution of data will be checked using the Shapiro-Wilk test. The level of significance will be set to *P*≤.05 (2-sided, uncorrected).

For all demographic variables, between-group differences (ie, intervention vs control) will be tested using an independent *t* test or Mann-Whitney *U* test in case the data are not normally distributed. For primary and secondary outcomes, the assumption of homogeneity of variance will be checked using Levene test. In case all assumptions for a 2-way analysis of covariance (ANCOVA) are met, effectiveness of the “Brain-IT” training will be analyzed using a two-way ANCOVA with the premeasurement value as covariate for the predicting group factor and the postmeasurement value as outcome variable [202]. If not all assumptions are met, the Quade nonparametric ANCOVA will be used. Because of the stratification by sex in the randomization process, no sex-specific statistical analysis will be computed. However, if there are relevant between-group differences in sex distribution or other demographic variables, these will be included in the statistical analyses as additional covariates. To determine whether the effects are substantive, partial eta-squared (η^2^_p_) effect sizes will be calculated for all primary and secondary outcomes. Effect sizes will be interpreted as small (0.01≤η^2^_p_<0.06), medium (0.06≤η^2^_p_<0.14), or large (η^2^_p_>0.14) [203].

Statistical analysis will be performed by PM after data collection is completed. As this is a small-scale RCT, no interim analysis will be performed.

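### The attrition allowance is too small: 20 per arm keeps 14 completers only up to 30% attrition, not 40%, and 17 per arm falls short at the anticipated 20%

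*Protocol article*

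**What the plan says.** All the figures are in the protocol article under Methods, Sample Size. The base number is given as "This leads to a justified optimal sample size of n=14 per arm". The attrition rate comes from the sponsor's pilot trial and several reviews: "Therefore, an attrition rate of 20% is anticipated". The section then adds that "a wide upper safety margin for an attrition rate of up to 40% is selected", with the declared aim of ensuring enough participants. Its conclusion is that "we will aim to recruit 17 to 20 older adults with mNCD per group, leading to a total sample size of 34 to 40". No inflation formula is written out. The trial registration table (Table 1) gives a target sample size of 40.

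Statistical Methods defines who counts towards the 14. For the primary and secondary outcomes, "the data of all participants who completed pre- and postintervention measurements, regardless of protocol adherence, will be included in the statistical analyses". A participant who drops out before the second measurement therefore does not contribute.

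**The concern.** Attrition is a fraction of the people recruited. To end with a given number of completers, that number must be divided by (1 − rate). The stated targets look as if 14 was multiplied by (1 + rate) instead. The two calculations nearly agree at low rates and separate quickly as the rate rises, so the error matters most at the upper margin.

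If so, the protocol presents a safeguard that the design lacks. The 14 per arm is the number the sponsor justified for estimating the treatment effect precisely enough to plan a full-scale trial. The upper target would miss it at the attrition it is said to withstand, and the lower target would miss it at the attrition the sponsor expects.

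**Working it through.** **Inputs** (Sample Size, unless noted)
- Completers needed per arm: 14. This is taken as given. It comes from a cited source that is not at hand, and the attrition step does not depend on how it was reached.
- Anticipated attrition: 20%. Upper margin: 40%.
- Recruitment target: 17 to 20 per arm, 34 to 40 in total, allocated 1:1 (Sequence Generation).
- Analysis set: participants with both measurements (Statistical Methods).

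**Step 1. Reproduce the stated targets.** Multiplying by (1 + rate):
- 14 × 1.20 = 16.8, rounded up to 17
- 14 × 1.40 = 19.6, rounded up to 20

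Both ends of the stated range come out exactly.

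**Step 2. Number needed to keep 14 completers.** Dividing by (1 − rate):
- 14 / 0.80 = 17.5, so 18 per arm (36 in total)
- 14 / 0.60 = 23.3, so 24 per arm (48 in total)

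Neither stated end is reproduced.

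**Step 3. Completers expected from the stated targets.** Recruited × (1 − rate):

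| Recruited per arm | Attrition | Expected completers per arm |
|---|---|---|
| 17 | 20% | 13.6 |
| 20 | 20% | 16.0 |
| 20 | 40% | 12.0 |

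At 20 per arm and 40% attrition the total is 24 completers, against the 28 needed.

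**Step 4. Attrition each target can absorb.** 1 − 14/recruited:
- 17 per arm: 1 − 14/17 = 17.6%
- 20 per arm: 1 − 14/20 = 30.0%

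**Step 5. Chance of reaching the number.** This step assumes that participants drop out independently, at the same rate in both arms, so that completers are binomial. The protocol does not say whether 14 must be met in each arm or 28 overall, so both are shown.

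| Recruited per arm | Attrition | At least 14 in one given arm | At least 14 in both arms | At least 28 in total |
|---|---|---|---|---|
| 17 | 20% | 55% | 30% | 47% |
| 20 | 20% | 91% | 83% | 96% |
| 20 | 40% | 25% | 6% | 13% |

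The both-arms column is the square of the one-arm column before rounding. The ordering is the same under every criterion.

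**The case against.** The strongest reply is that the defect is narrow and its consequence small.

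- *Only one number fails at the expected rate.* At 20% attrition, 18, 19 and 20 per arm give 14.4, 15.2 and 16.0 expected completers. Only 17 misses, by 0.4 of a participant, and the registered target of 40 means 20 per arm. This stands. The weight of the point lies at the 40% end, where the gap of four per arm cannot be rounding.
- *The formula is inferred.* The article writes none and does not explicitly pair 17 with 20% or 20 with 40%. This also stands, although the inferred formula gives both ends exactly. The shortfall does not depend on it, since no number in the range 17 to 20 keeps 14 completers at 40%.
- *The both-arms probability is a strict test.* By that test even the corrected numbers look modest: 51% for 18 per arm at 20%, and 42% for 24 per arm at 40%. This is fair. The probabilities should be read as comparisons between designs, and any statement of protection holds in expectation only.
- *The precision lost is small.* If the standard error scales as 1/√n, 12 completers instead of 14 widen it by √(14/12) − 1, about 8%; 13.6 instead of 14 widen it by about 1.5%. The Limitations section already concedes that the analyses will probably be underpowered. This limits the harm, but that concession concerns hypothesis tests, and it rests on the sample size having been justified for precision.
- *Attrition of 40% is unlikely.* The reviews cited average 10% to 17%. But the sponsor chose the margin, and the ranges cited reach 31% for exergame-based interventions and 59% for physical training. Both exceed the 30% that 20 per arm covers.

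**Conclusion.** The concern holds. The stated protection against attrition of up to 40% is wrong. The largest target covers 30%, and 40% would need 24 per arm (48 in total, eight more than planned). The smallest target is one per arm short of the 18 needed at the anticipated 20%. A target of 20 per arm is adequate at that rate.

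This rests on two readings of the document: that 14 per arm means analysable participants, which follows from the analysis set, and that the attrition rate is a share of those recruited, which is its ordinary meaning. The expected-value results need no further assumption. The binomial probabilities also assume independent dropout at equal rates in the two arms. The practical effect is on the precision of the estimate used to plan the full-scale trial. No endpoint or analysis method is affected.

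**What to change.** Correct the Sample Size section in one of two ways.

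1. **Keep the trial at its registered size (preferred).** Fix the target at 20 per arm in place of the 17 to 20 range. State that, in expectation, this leaves 14 completers per arm for attrition up to 30%. If a lower bound is still wanted, make it 18 per arm, the minimum for 20% attrition; 17 per arm covers only about 17%. The cost is a corrected sentence and a stated margin that falls from 40% to 30%. Nobody is recruited beyond the 40 already registered.
2. **Keep the 20% to 40% claim.** Change the target to 18 to 24 per arm, 36 to 48 in total. This costs up to eight participants more than planned, and the registered target of 40 would have to be updated.

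In either case, write out the formula, recruited = 14 / (1 − attrition rate), so that the allowance can be checked.

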### Randomization

#### Sequence Generation

Participants will be randomly allocated to the intervention or control group. Variable block randomization (ie, block sizes=4, 6, and 8) with a 1:1 allocation ratio stratified by sex and institute (study center) will be used.

#### Allocation Concealment Mechanism

To ensure allocation concealment, random allocation will be computer generated using a validated variable block randomization model implemented in the data management system Castor EDC (Ciwit BV) [201].

#### Implementation

Randomization process will be set up by PM before starting patient recruitment. PM will also oversee the enrollment of participants. Participants will individually be assigned to the intervention or control group by the investigator responsible for supervision and correspondence with the respective study participant after completing premeasurements. Randomization allocation can be viewed in eCRFs by investigators who have been assigned right to do so. The eCRF is implemented in the Castor EDC data management system [201]. None of the investigators performing postintervention measurements will have access rights to view the randomization allocation in eRCFs.

